### Sample size

This is an exploratory study designed to include 80 subjects with clinically stable COPD (assuming a 10–20% drop-out rate) to accommodate various degrees of biological variations in the different exploratory outcome measures. Of these, 20 will also undergo bronchoscopy. Findings that do not reach statistical significance in a sample size of approximately 80 subjects are likely to have limited clinical relevance.

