**Methods:**

This is the protocol of a multicenter, hypothesis-generating, single-arm study exploring the mechanisms for lung regeneration in subjects with COPD induced by exercise. The exercise protocol includes supervised and individually tailored moderate-intensity aerobic- and muscle strengthening exercise, performed three times per week for 12 weeks. Eighty sedentary adults with a clinically stable COPD will be recruited at two study sites. Included participants will be assessed at baseline and at 12 weeks by comprehensive pulmonary function testing (including spirometry, IOS, body plethysmography, diffusing capacity of the lung, single breath nitrogen wash-out, AiDA, questionnaires, physical capacity performance (including 6-minutes walking test (6MWT), one-minute sit-to-stand test, and cardiopulmonary exercise testing (CPET)), and collection of blood and urine samples and bronchoscopy. A mid-intervention assessment at week 6 will include medication use, health status, questionnaires, spirometry, and blood sampling.

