### Study outcomes

The primary outcome is to validate the effect in protein profiles after exercise intervention in lung tissue biopsies, blood- and urine samples using proteomic analyses such as multi-plex ELISA, OLINK, and mass spectrometry. Primary factors include; matrix turnover/remodelling proteins: MMPs, TIMPs, MMP-degraded collagen peptides, desmosine, periostin, decorin; growthfactors: VEGF, HGF, PDGF, FGF-2, angiopoietin; inflammatory/immune markers: TNF-a IL-6, IL1-b, IL-8, IL-10, IL-17, MCP-1, CXCL10, CXCl13.

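### The sample-size section links non-significance in about 80 subjects to limited clinical relevance; nothing stated supports this, and the tissue part of the primary outcome has only 20 participants

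*Protocol article*

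**What the plan says.** The Sample size section of the protocol article sets the number in three sentences.

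- Enrolment: "This is an exploratory study designed to include 80 subjects with clinically stable COPD", with the qualifier "assuming a 10–20% drop-out rate". The reason given is qualitative: to allow for biological variation across the outcome measures.
- Bronchoscopy: "Of these, 20 will also undergo bronchoscopy".
- Interpretation: "Findings that do not reach statistical significance in a sample size of approximately 80 subjects are likely to have limited clinical relevance".

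The Study outcomes section defines the primary outcome as the aim to "validate the effect in protein profiles after exercise intervention in lung tissue biopsies, blood- and urine samples". Tissue is therefore one of its three sample types. Statistical methods specifies paired testing of the change from baseline to post-intervention, two-sided, with alpha 0.05.

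The Methods paragraph of the abstract lists the baseline and 12-week assessments of included participants and ends that list with "and collection of blood and urine samples and bronchoscopy". It does not mention a subset.

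**The concern.** A non-significant result supports a claim of limited relevance only if the study had high power against a change defined in advance as relevant, or if the confidence interval (CI) excludes such a change. The sentence makes the claim without either. The article gives minimal important differences for CAT, CCQ, the six-minute walk, the sit-to-stand test and VO2, but not for any protein, and proteins are the primary outcome.

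The sentence also rests on about 80 subjects directly after the text has limited bronchoscopy to 20. Tissue results never come near the number on which the reassurance depends. A reader of the abstract alone could think that they do.

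The main objective is to identify mechanisms of lung regeneration, and tissue is direct evidence for that. If the remark guided the reading of results, an inconclusive tissue finding could be taken as a negative one. In a hypothesis-generating study, that closes off leads too early.

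The point is not that a power calculation is missing. An exploratory study may do without one, and an analysis plan may hold more detail. The point is that the article makes a claim about relevance which its own figures do not support.

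**Working it through.** **Plan's own figure.** The number 80 cannot be reproduced, because no effect size, SD or power stands behind it. What can be computed is what the stated numbers deliver.

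**Inputs from the article.** Enrolment 80, drop-out 10–20% and bronchoscopy subset 20 (Sample size); paired test, two-sided alpha 0.05 (Statistical methods).

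**Assumptions.** (a) 80 means enrolled. (b) For the 16–18 figure only, the overall drop-out also applies to the bronchoscopy subset; the article does not say so, and 20 could mean completed pairs. (c) Effects are in SDs of the individual change, dz = mean change / SD of change, because no SD is given.

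**Step 1: pairs.**
- Blood and urine: 80 × 0.80 = 64; 80 × 0.90 = 72.
- Tissue: 20 if all complete; 20 × 0.80 = 16 and 20 × 0.90 = 18 under assumption (b).

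**Step 2: precision.** The 95% CI half-width in SDs of change is t(0.975, n−1)/√n. It is also the smallest observed dz that reaches p < 0.05. For n = 20: 2.093/√20 = 0.468. For n = 64: 1.998/√64 = 0.250.

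**Step 3: power.** Power is the probability that a noncentral t variable with n−1 degrees of freedom and noncentrality dz·√n falls beyond the critical value.

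| Pairs | CI half-width (SD) | dz with 80% power | Power at dz 0.3 | Power at dz 0.5 |
|---|---|---|---|---|
| 16 | 0.533 | 0.749 | 0.20 | 0.465 |
| 18 | 0.497 | 0.701 | 0.22 | 0.516 |
| 20 | 0.468 | 0.660 | 0.25 | 0.564 |
| 64 | 0.250 | 0.356 | 0.66 | 0.976 |
| 72 | 0.235 | 0.335 | 0.71 | 0.987 |
| 80 | 0.223 | 0.317 | 0.76 | 0.993 |

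**Step 4: misses at a true 0.5 SD change in tissue.** 1 − 0.564 = 43.6% with 20 pairs; 1 − 0.516 = 48.4% with 18; 1 − 0.465 = 53.5% with 16.

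**Step 5: blood and urine.** Power at dz 0.4 is 88–92% and at dz 0.5 is 98–99% with 64–72 pairs. It falls to 66–71% at dz 0.3 and to 35–39% at dz 0.2. Even with a full 80 pairs, dz 0.2 has only 42%.

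**Step 6: outcomes that have a stated threshold.** The SDs of change here are assumed, since the article gives none. With 64–72 pairs, a 2-unit CAT change has 98–99% power at SD 4, 75–80% at SD 6 and 50–55% at SD 8. A 30 m change in the six-minute walk has 98–99% power at SD 60 m and 66–71% at SD 100 m. Whether the remark is roughly right therefore depends on an SD that the article does not state.

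**The case against.** The strongest defence is about scope. The sentence is hedged, speaks of about 80 subjects, and sits in a sample-size justification. A reader might infer that the protocol has a rule under which non-significant findings, tissue findings included, will be discarded. The documents do not support that reading. Statistical methods contains no such rule, Dissemination plans commits to reporting whatever the size or direction of the effect, and Trial design calls the study exploratory and hypothesis-generating. Read literally, the sentence does not cover results from 20 participants. This part of the defence stands: the harm is something that could follow if the remark were used in interpretation, not something that the plan prescribes.

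A reader might also infer that blood and urine are badly underpowered. They are not: changes from about 0.4 SD are well covered, and for clinical outcomes with a threshold the remark may be close to right under moderate assumed SDs.

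It can also be said that 16–18 tissue pairs rest on a drop-out rate stated for the whole cohort. That is correct, so the figure for 20 pairs is given first. The conclusion barely moves, since the detectable change is still 0.66 SD.

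Finally, the abstract may simply be condensed. That is plausible, and the mismatch is minor. It matters here only because it hides how few participants supply tissue.

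None of this gives the sentence a basis. No stated quantity connects significance at this number with a relevant change in any protein.

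**Conclusion.** The concern holds as a wording-level correction. The remark claims a property that the stated design is not shown to have, and its number does not apply to the tissue part of the primary outcome. The weakness is clearest in tissue, where the 80%-power threshold is about twice that for blood and urine (0.66/0.34 = 1.9; 0.75/0.36 = 2.1) and a half-SD change is missed in roughly half of trials. In blood and urine, only changes below about 0.35 SD are at real risk.

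The figures assume an unadjusted paired t-test at two-sided 0.05 for a single marker, and that 80 is the enrolled number. If 80 were evaluable, the detectable change would be 0.32 SD and the conclusion would be the same. No endpoint, test or sample is invalid because of this sentence.

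**What to change.** 1. Delete the sentence on non-significant findings from the Sample size section.
2. In its place, state the expected pairs and 95% CI half-widths by sample type: blood and urine 64–72 pairs, about 0.24–0.25 SD of change; tissue 20 pairs, about 0.47 SD, or 16–18 pairs, about 0.50–0.53 SD, if the overall drop-out is assumed for the subset. Label that assumption, or say that 20 means completed pairs.
3. Say that non-significant results will be reported with their CI and described as inconclusive, not as lacking relevance.
4. Reconcile the abstract's assessment list with the 20-participant bronchoscopy subset.

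A rule that reserves a statement of limited relevance for CIs lying wholly inside a stated minimal important difference would be an optional addition; if used, it should cover VO2 as well as the other four measures. The required changes are text only. No sample, visit, procedure or test changes, and recruitment is not affected. The price is that the stated precision for tissue will look less favourable than the present wording suggests.

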### Recruitment procedure

Participants diagnosed with COPD will continuously be recruited from primary and specialist care in and around Lund/Malmö and Uppsala regions in Sweden. We will also advertise through, for example, social media and patient organizations (e.g., the patient associations) as well as advertising in local and national newspapers. Telephone screening will be used to identify and invite eligible participants for inclusion in the study.

### Trial status

The study is currently recruiting participants.

### Plans for assessment and collection of outcomes

The assessment and collection of data will be conducted by specially trained research nurses with extensive experience of performing the study related assessments and collecting data from participants. All testing is done according to standardized procedures and with validated protocols. All equipment fulfils standardized requirements. The basic baseline assessments will be carried out before (initial visit) and after the completion of the training program (follow-up visit post-training program), as well as a less comprehensive examination after halfway through the training program.

### Plans to promote participant retention and complete follow-up

Plans to promote participant retention will include frequent contact with study team including calls for symptom checks, and reminder calls prior to scheduled study visits. We will aim to collect as much outcome data as possible in participants who discontinue or deviate from the protocol, including detailed records of reasons for discontinuation.

### Data management

We will use the Research Electronic Data Capture system (REDCap), which is offered to affiliated research group leaders at the Faculty of Medicine at both Lund and Uppsala universities to collect, store and report clinical research data in a secure manner. To ensure data accuracy and confidentiality, all data will be initially recorded on paper Case Report Forms (CRFs), then verified and entered into REDCap by data management personnel. Consenting participants will be assigned a unique sequential participant identification code which will be used to pseudonymize all data. This study ID number will be used in all data collection and analyses. All personal data will be processed in accordance with the EU General Data Protection Regulation (GDPR). Code list, paper CRF and signed informed consents will be stored in a locked cabinet in the respective research centers.

### Statistical methods

After the last participant has completed all assessments, additional monitoring and data quality checks will be completed. Analyses will be performed by the investigators supported by a biostatistician when needed. All statistical tests will be conducted as two-sided, with the alpha level set at 0.05. Baseline variables and descriptive statistics with continuous data will be presented with mean ± standard deviation (SD) or median with interquartile range (IQR) as appropriate. Ordinal variables will be presented as median (IQR), and categorical variables will be presented as n (%).

Continuous data with normative values (for example lung function values) will be presented both as absolute values and as % of predicted normal values.

The primary outcome is the change from baseline to post intervention, and analyses will be performed with paired statistical testing. Analyses of both absolute change (delta values) and % change will be performed. Age, sex, pack-years and site are potential confounding factors which might be taken into account as co-variates.

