### Impulse oscillometry (IOS)

IOS provides information about the mechanical properties of large and small airways (Jaeger MasterScreen IOSHoechberg, Germany). Resistance is estimated at 5 Hz (R_5_, reflecting total resistance) and at 20 Hz (R_20_, reflecting central resistance), while R_5_-R_20_ is subsequently calculated and reflects peripheral resistance. Airway reactance (elastance) of the lung is estimated at 5 Hz (X_5_), which during small airway obstruction gives a more negative value, while the resonant frequency (F_res_) increases together with the area under the reactance curve (AX), which is measured from 5 Hz to F_res_. The test is performed in an upright position and the subjects hold their hand palms on their cheeks to stabilize the upper shunt [34]. The mean of three accurate measurements of 30 s is recorded.

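### Percent change from baseline is put on an equal footing with absolute change for the primary protein markers, although mean % change is biased upward when nothing changes

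*Protocol article*

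**What the plan says.** Under Study outcomes, the primary outcome is given as follows: "The primary outcome is to validate the effect in protein profiles after exercise intervention in lung tissue biopsies, blood- and urine samples". The markers listed include matrix turnover proteins and "growthfactors: VEGF, HGF, PDGF, FGF-2, angiopoietin; inflammatory/immune markers: TNF-a IL-6, IL1-b, IL-8, IL-10, IL-17, MCP-1".

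Under Statistical methods: "The primary outcome is the change from baseline to post intervention, and analyses will be performed with paired statistical testing". The error rate is set for every test: "All statistical tests will be conducted as two-sided, with the alpha level set at 0.05". The next commitment is the one at issue: "Analyses of both absolute change (delta values) and % change will be performed". The section does not say which of the two scales carries the conclusion, whether the paired test is parametric or rank-based, or whether concentrations are log-transformed. Median and IQR are mentioned for descriptive presentation only.

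Under Sample size, 80 participants are planned with 10 to 20% drop-out, and 20 of them have bronchoscopy. Under Trial design, the study is a single group.

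**The concern.** Percent change divides the follow-up value by one noisy baseline value. A baseline that happens to be low inflates the ratio by more than an equally high one deflates it, so the average % change is positive when nothing has happened. Cytokines, proteases and growth factors are positive and are assumed here to be right-skewed, which is the setting where this matters most.

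Two things are at stake. For growth factors, a spurious rise could be read as regeneration activated by exercise. For inflammatory and matrix-degrading markers, where the trial expects a fall, the same bias can hide it. There is no control arm in which the same artefact would appear and cancel. The Sample size section also treats statistical significance as a guide to clinical relevance, so an inflated error rate would feed directly into which markers are carried forward.

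**Working it through.** **Plan's own figures.** The protocol gives no effect size, SD, power or within-person variability, so there is no stated operating characteristic to reproduce. Only the drop-out arithmetic can be checked: 80 × 0.80 = 64 and 80 × 0.90 = 72 completers. The same drop-out applied to 20 bronchoscopies gives 16 to 18 pairs.

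**Direction of the bias, without a distributional assumption.** Let r = post/pre, with pre and post positive and exchangeable (no true change). Then E[r] = E[1/r], so E[r] = E[(r + 1/r)/2]. Because (r + 1/r)/2 ≥ 1 for every positive r, E[r] ≥ 1, with equality only if there is no within-person variation. Mean % change is therefore above zero under no effect.

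**Size, if log-normal (assumption).** Write σ² for the within-person variance on the log scale, so CV² = exp(σ²) − 1. Then E[post/pre] − 1 = exp(σ²) − 1 = CV². For CVs of 10, 20, 30 and 50% the spurious mean change is +1, +4, +9 and +25%.

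**Rough check of the rejection rate.** The SD of the ratio is (1 + CV²) × √[(1 + CV²)² − 1]. At CV 30% this is 1.09 × √(1.1881 − 1) = 0.473. With 64 pairs the expected t is about 0.09 × √64 / 0.473 = 1.52, and the chance of exceeding 1.96 is roughly 1 − Φ(0.44) = 33%. Simulation, which allows for the skewness of the ratio, gives 29%.

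**Simulated rejection rates.** No true change, log-normal values, between-person CV 60% (assumed), two-sided 0.05, one-sample t-test on % change:

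| Within-person CV (assumed) | Mean % change | n = 64 | n = 72 |
|---|---|---|---|
| 10% | +1% | 7.6% | 8.3% |
| 20% | +4% | 16.1% | 18.3% |
| 30% | +9% | 29.4% | 32.9% |
| 50% | +25% | 57.8% | 64.1% |
| 80% | +64% | 81.9% | 87.4% |

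From CV 20% upward, nearly all rejections are increases. Repeated simulations agree to within about 2 percentage points.

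**Other cases, CV 20 to 50%.**
- Signed-rank test on % change: 8.0 to 17.7% (n = 64) and 8.9 to 19.5% (n = 72). The test does not remove the problem, because % change is not symmetric about zero under no effect.
- Bronchoscopy subset, t-test on % change: 5.7 to 9.0% (n = 16) and 6.6 to 12.6% (n = 20).
- t-test on absolute change: 4.0 to 5.0% at n = 64 and 72.
- Test on the log ratio: 4.8 to 5.2% at n = 64 and 72.
- Positive if either absolute or % change is significant: 18 to 60% (n = 64) and 21 to 67% (n = 72), only about 2 to 3 points above % change alone.

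**A true fall.** Suppose the geometric mean falls by 10%. At CV 30% the expected % change is 0.90 × 1.09 − 1 = −1.9%. With 64 to 72 pairs the log-scale test detects the fall in 51 to 56% of trials, and the t-test on % change in about 8%. At CV 50% the expected % change is 0.90 × 1.25 − 1 = +12.5%, and the % change test declares a significant increase in about one trial in six.

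**The case against.** The strongest reply is that the text does not fix a t-test on raw % change. It says only that testing is paired, and it allows medians for descriptive data. With skewed data a signed-rank test would be the usual choice, and a statistical analysis plan that is not shown may specify a test or a transformation. The study is also exploratory, and the absolute-change analysis alongside holds its level.

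Much of this stands. A reader might infer that the false-positive rate simply is 16 to 64% rather than 5%. The documents do not support that: it needs an assumed CV of 20 to 50%, a t-test and 64 to 72 pairs. A rank test, a small CV or the biopsy subset gives much lower rates. A reader might also blame the two chances of significance per marker, but these add only 2 to 3 points. Nor does the bias always favour the trial's hypotheses: for TNF-α, IL-6 or IL-8 it works against the expected reduction.

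For oscillometry, a reader might infer inflated error rates as well. The protocol says of X5 that small airway obstruction "which during small airway obstruction gives a more negative value", and of R5-R20 that it "is subsequently calculated and reflects peripheral resistance". A negative denominator reverses the sign of % change, and a difference near zero makes it unstable. These are reasons not to test that scale, but no error rate has been shown for either index.

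What does not stand is the appeal to the unseen plan. The protocol itself commits to analysing % change of the primary outcome without ranking it below absolute change, and a rank test only reduces the excess. An exploratory aim does not excuse an artefact with a known direction.

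**Conclusion.** The point holds in conditional form. Raw % change is a poor tested scale for the primary protein markers because its mean is above zero under no effect, and the single-arm design cannot reveal this. The direction needs only positive values, within-person variation and exchangeability of pre and post under no effect. The size rests on log-normality and on within-person CVs that the documents do not give. With 64 to 72 pairs and CVs of 20 to 50%, about 16 to 65% of null tests reject with a t-test and about 8 to 20% with a signed-rank test. The t-test rate is about 8% at a CV of 10%, and about 6 to 13% with 16 to 20 bronchoscopy pairs at CVs of 20 to 50%. Absolute change and the log ratio stay near 5%. It is a should-fix point: the sound analysis is already partly present, and the remedy is to say which scale counts.

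**What to change.** Replace the sentence on absolute and % change with one that names a single tested scale per outcome.

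- **Protein markers:** test the change in log concentration, leaving assay units that are already logarithmic as they are. Report the geometric mean post/pre ratio with its 95% CI, displayed as a percentage. Keep raw % change as a descriptive figure only.
- **Lung function and physical tests:** name one tested scale for each outcome, consistent with how its MCID is expressed. The protocol gives the VO2 MCID as 5 to 10%, so a relative scale is reasonable there; the 6MWT and sit-to-stand MCIDs are in absolute units. A blanket rule of absolute change only would not fit.
- **Oscillometry:** do not test raw % change for X5 or R5-R20.

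The cost is one or two sentences in the statistical methods or analysis plan. No data collection changes, and the number of tests falls. The downside is a small loss of familiarity in reporting, eased by showing the geometric mean ratio as a percentage. The protocol says the trial is still recruiting and that analysis follows the last assessment, so the change can be made beforehand.

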### Data monitoring

Participants will be monitored by physiotherapists during training sessions to identify signals that would require interruption of the session or exclusion from the trial. All lung function testing and CPET will be supervised by experienced nurses or biomedical technicians, and all data will be interpreted by specialists. A data monitoring committee is composed of the responsible researchers, physicians and physiotherapists, and will discuss adjustments to individual tasks. All data analysis is independent of a sponsor.

Any significant protocol modifications, including changes to the study aims, primary outcomes, design, sample size, or statistical analysis, will be reported to the Ethics Committee that authorized the trial. Additionally, these modifications will be updated in the ClinicalTrials.gov registry and transparently documented in trial reports and publications.

